#### Population of case-matched general population controls

For each case, two individuals of the same sex as the case will be selected from the general population who were registered in the same National Health Applications and Infrastructure Services (NHAIS) system as the case at the case's date of *index diagnosis*, were alive at the case’s date of *index diagnosis*, were born within 1 month either side of the case’s date of birth, and had had their first invitation to bowel screening in the same year as the case. If no matched control is found for a particular case with a date of birth within 1 month either side of the case's date of birth, the range will be expanded to 3 months either side (or 6 months either side if the case’s age at *index diagnosis* of primary CRC is over 75). For subsequent phases of this evaluation (main phase onwards), they will not have been included as population controls in previous evaluation periods.

Incident advanced stage cases and matched general population controls will be selected a posteriori by the PRU according to various designs as described in Table 1. In the initial stages of the evaluation, incident cases will be restricted to those individuals with Duke’s stage B or worse primary CRC at *index diagnosis* (Designs 1–3). Data permitting, we will also include individuals diagnosed with a Duke's stage A primary CRC during the study window but who were subsequently found to develop metastases (i.e. the cancer becomes stage B or worse) in order to avoid introducing a bias *in favour* of screening by excluding them from the population of cases and underestimating the proportion of Duke B+ tumours among screen-detected. Indeed, metastases are more likely to be early and therefore minimal and so missed in screen-detected compared to symptomatic cases; as a consequence, a minority of screen-detected tumours may be classified as having a less advanced stage leading to the underestimation of screening exposure in cases, and creating a bias *in favour* of screening.

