**Design 5**			
	Previous diagnosis	None	None
		CRA	CRA
	Index diagnosis	Any CRC (Duke A-D)	_
		Screen-detected	Last screened in same year as case index screen
	Analysis	Exposure to screening prior to *index diagnosis* of case	
		Controlling for previous history of CRA	

CRA: Colorectal Adenoma; CRC: Colorectal Cancer.

Duke A CRC: CRC diagnosed at stage Duke A; Duke B+ CRC: CRC diagnosed at stage Duke B, C or D.

Matched general population controls will be restricted to those individuals who have never had stage B or worse primary CRC, but may have had early stage primary CRC (Duke’s stage A) or CRA prior to and including the case's date of *index diagnosis*. The majority of controls, will, however, never have had CRC (or CRA). In later stages of the evaluation, all incident cases will be considered (Design 4).

All cases and controls will appear on the HSCIC database at Exeter and will have available data on bowel, cervical (for women aged 60–64) and breast (for women aged 60–74) screening strictly prior to the date of *index/first diagnosis* of the case, depending on the analysis (that is, they have been invited to screening at least once prior, see Table 1 for details). Bowel, cervical and breast screening history as well as primary CRC pathology variables will be retrieved for all cases and controls. In addition, history of previous CRA and corresponding tumour pathology variables will be obtained.

A detailed description of the subject selection criteria and matching algorithm will be created in collaboration with our NHS partners.

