#### Exposure opportunity (frequency) bias

Once diagnosed with cancer, the cases come under clinical management and do not continue with routine screening as before. The controls, however, will continue to attend screening. To avoid a potential bias *in favour* of screening, controls are given a pseudo-diagnosis date that is the same as that of their matched case and screening history is only considered up to that date [29].

In contrast, the fact of the case having necessarily a diagnosis of cancer and a control usually not having such a diagnosis, induces an artificially higher retrospective probability of screening exposure in the cases, a bias *against screening* (i.e. the screen-detected cases will always have this screen recorded at diagnosis, whereas the large majority of controls will not at pseudo-diagnosis date). Simply excluding the detection screens of the cases from the histories would bias the results *in favour* of screening. A driver of this bias is prevalence screening and, as the NHS BCSP is a relatively young programme with at most 3 rounds at the planned start of the pilot phase (January 2012), this bias may initially be present although it is likely to decrease for subsequent evaluations.

The extent of screening opportunity bias will be investigated first, by applying an analytical correction to the odds ratio using the method developed by Duffy and collaborators [30], and second, by performing sensitivity analyses in which the date of pseudo-diagnosis for controls whose matched cases have had a screen-detected *index diagnosis* will be extended by up to 3 years, the estimated average sojourn time for each screen-detected case, to counteract the artificially higher retrospective probability of screening exposure in cases [29]. A shorter sojourn time may however be more appropriate for screen-detected tumours of stage Duke B or worse [31].

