In addition, we will perform a sensitivity analysis using screen-detected cases only. We will aim to establish whether such cases were screened less often in the past than matched controls who were screened at the time of detection screen of the case [32, 33]. In this analysis, controls that have had a screen in the same year as the *index screen* (detection screen) of their matched case will be included. The *index screen* will be excluded and the effect of prior attendance at screening on incidence of advanced stage primary CRC will be investigated. The impact of being invited to bowel cancer screening prior to *index screen* on CRC incidence may also be investigated.

But the major source of bias in case–control studies where controls are selected from the general population is potential self-selection bias [34].

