### Statistical methods

Case–control study analyses will be conducted using conditional logistic regression. Matching factors (i.e. age, area and year of first invitation to bowel cancer screening) are controlled for in design, and additional analyses will be stratified by sex and anatomical subsite. All statistical analyses will be performed using the statistical software STATA version 12 and/or R version 2.13.0.

The ***primary objective*** of this case–control will be to assess the effect of various measures of participation in bowel cancer screening *strictly prior to* the case’s date of *index/first diagnosis* on incidence from advanced stage primary CRC (see details in Table 1). The primary measure of participation to screening will be whether an individual ever attended at least one screen episode prior to diagnosis. Secondary measures will be the total number of screens, the time since last screen, the time since penultimate screen, the interval between last screen and penultimate screen, the maximum interval between 2 screens, the average interval between 2 screens, the total number of invitations, the patient's age at first screen, and the patient’s age at last screen.

‘Time since last screen’ will give estimates of the likely benefit of screening at different intervals. It will include whether that time span fell within the past two years, as this corresponds to the NHS BCSP interval and approximates the estimated preclinical screen-detectable period (PCDP).

***The secondary objective*** will be to consider the effect of screening on overall CRC incidence, regardless of stage. Similar measures of participation will be used.

*Self-selection* and *exposure opportunity* biases will be addressed using the methods described in the *Bias & Effect modification* section.

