Secondary analyses will consider time since last screen stratified by age at diagnosis/pseudo-diagnosis, by *index/first tumour* detection mode, and by region (Main phase only). Analysis may be adjusted for stage at diagnosis. The effect of attending a screen in a particular 5-year age band (e.g. 60–64), in the pilot phase, or 2-year age band (e.g. 60–61), in the main phase, on incidence from advanced stage primary CRC in the subsequent 5-year age band (i.e. 62–66 or 65–69, respectively) will also be investigated, as performed for the cervical screening audit [17]. The results of this analysis should be very similar to those obtained from the analysis of ‘time since last screen’ after stratifying the analysis by age at diagnosis/pseudo-diagnosis.

In the main phase of the study, the effect of invitation to bowel screening and attendance at screening prior to the *index screen* of the case will also be assessed among screen-detected cases matched to controls screened within the same screening interval (Table 1 Design 5).

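### Matching on year of first invitation leaves Design 5 no usable contrast for prior invitation, and very little for the number of invitations

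*Protocol article*

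**What the plan says.** **Planned invitation analyses**
- Statistical methods, last paragraph: in the main phase, "the effect of invitation to bowel screening and attendance at screening prior to the" index screen will be assessed among screen-detected cases. The sentence refers to Table 1 Design 5 and describes the controls as screened within the same screening interval.
- Exposure opportunity (frequency) bias: "The impact of being invited to bowel cancer screening prior to" the index screen may also be investigated, in an analysis whose controls had a screen in the same year as the case's index screen.
- Statistical methods, secondary measures: "the total number of invitations" is one of the listed exposures.

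**Matching and eligibility**
- Population of case-matched general population controls: controls are of the same sex, "registered in the same National Health Applications and Infrastructure Services (NHAIS) system as the case", "were born within 1 month either side of the" case's birth date (widened to 3 months, or to 6 months for cases over 75, if no match is found), and "had had their first invitation to bowel screening in the same year as the case".
- Text after Table 1: all cases and controls must be such that "they have been invited to screening at least once prior" to the relevant diagnosis date.
- Exposure opportunity (frequency) bias: "controls are given a pseudo-diagnosis date that is the same as that of their matched case", and histories stop there.
- Table 1, Design 5: the control's last screen falls in the calendar year of the case's index screen.
- Statistical methods: the analysis is conditional logistic regression, and year of first invitation is described as controlled by design.

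**The concern.** Conditional logistic regression learns only from matched sets in which case and control differ on the exposure. When a design matches on the year a person entered the programme, stops both histories on the same date and admits only people already invited, it has largely fixed invitation history before the analysis starts. The plan nevertheless treats invitation before the index screen, and the invitation count, as exposures.

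For prior invitation in Design 5, a committed main-phase analysis would return an undefined odds ratio, or one resting on a handful of irregular records. For the invitation count the risk is different. A national sample could give a fairly precise odds ratio that readers take as the effect of the programme's offer, when the contrast behind it is mostly one of dates around the cut-off.

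**Working it through.** **Reference figure.** The protocol gives no discordance figure for invitation. Its only one is for attendance in Table 3: 20% + 16% = 36% of pairs discordant (39% + 25% = 64% concordant).

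**Step 1: prior invitation in Design 5, same-year rule.** Let F be the calendar year of first invitation and Y the calendar year of the index screen. Both are equal within a set. With recall every two years, the invitation of round k (k = 0 for the first) falls in year F + 2k. Assume the screen follows its invitation by no more than a year. Then Y is either F + 2k or F + 2k + 1, so

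k = integer part of (Y − F)/2.

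This is the same number for case and control. If Y − F is 0 or 1, neither had an invitation from an earlier round. If Y − F is 2 or more, both had one. Example: F = 2010 and Y = 2012 gives k = 1 for both; F = 2012 and Y = 2013 gives k = 0 for both. A simulation with invitation-to-screen delays of up to 0.25, 0.5 and 1 year found 0% discordant pairs each time. Reading the exposure literally, as any invitation before the index screen, does not help: anyone screened in response to an invitation is exposed.

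**Step 2: prior invitation in Design 5, same-interval rule.** Read loosely as screens less than two years apart, the simulation gives about 14% discordant pairs. It assumed first-invitation year uniform over 2006–2013, index screens in 2012–2013, screening equally likely at any of the first four rounds, and delays up to three months. The discordance arises because the control's screen may come from the neighbouring round of the same schedule.

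**Step 3: total number of invitations.** Let d be the gap in years between the two first-invitation dates. Matching on calendar year makes d less than 1, which is below the two-year interval, so the counts differ by at most one. They differ only when the shared cut-off falls between the two people's recall dates. For a cut-off uniform over a two-year period,

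P(discordant) = E(d)/2.

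- Dates independent within the year: E(d) = 1/3, so P = 1/6 = 16.7% (simulated 16.7%).
- Dates following birth dates matched to ±w years, within the same calendar year: E(d) = (w²/2 − w³/3)/(w − w²/2).

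| w | E(d) | P | Simulated |
|---|---|---|---|
| 1/12 (1 month) | 0.041 | 2.1% | 2.1% |
| 3/12 (3 months) | 0.119 | 6.0% | 6.0% |
| 6/12 (6 months) | 0.222 | 11.1% | 11.1% |

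Without matching on year of first invitation (dates independent and uniform over 2006–2011), the simulation gives about 70%.

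**Step 4: does 2% mean no estimate?** Take the protocol's 33,218 cases for 2010, two years, and its 56% qualifying fraction: 2 × 33,218 × 0.56 = 37,204 cases. At 2.07% (the simulated value for ±1 month), 37,204 × 0.0207 = about 770 discordant pairs with one control per case. This is illustrative and generous, because the national count is not restricted to ages 60–89. It shows that the count remains estimable.

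**The case against.** **The number of invitations is not inestimable.** A reader might infer from the matching that this effect cannot be estimated either. The documents do not support that: matching is on calendar year rather than date, and Step 4 shows that many discordant pairs could remain, with a second control per case adding more. This stands. It does not rescue the interpretation, because those pairs differ by one invitation falling just before or just after the cut-off.

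**The zero depends on one of two stated control rules.** This also stands. A reader might infer that no Design 5 set can be discordant under any reading, but the same-interval wording could allow about 14%. However, that sentence points to Table 1 Design 5, which states the same-year rule, and the extra discordance reflects which round the control's screen is taken from, not a difference in what the programme offered.

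**Birth date matching is looser than one month and may not govern invitation dates.** Correct: the window can widen, and no section says that invitations follow birthdays. The argument rests on year of first invitation and the shared cut-off. Birth date only moves the count's discordance within the 2% to 17% range.

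**Remaining discordance might be put down to follow-up of earlier findings.** A reader might infer this, but the documents do not establish it, and Table 1 controls for previous adenoma in every design and for previous cancer where it is allowed.

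**The detailed matching algorithm is deferred, and these analyses are secondary.** Both true. But the protocol says that the Table 1 designs are selected afterwards from the matched cases and controls, so the matching should carry over to Design 5. The invitation count is listed as a measure of participation and is not called a policy effect. This limits how serious the point is, but does not remove it.

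**Conclusion.** The point holds in two parts of different strength.

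- **Prior invitation in Design 5:** under the same-year rule there is essentially no within-set variation (0% discordant, against 36% assumed for attendance), so the planned effect cannot be estimated by conditional logistic regression. This assumes regular two-yearly recall, a screen within a year of its invitation, and the general matching carrying over to Design 5. Irregular recall, house moves or self-referral could create occasional exceptions.
- **Total number of invitations:** estimable but severely over-matched. It differs by at most one, in roughly 2% to 17% of pairs under regular recall, against about 70% without matching on year. What remains is mainly timing around the cut-off, which is open to the exposure opportunity problem that the protocol itself describes. It is not the effect of being offered screening.

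The primary exposure (ever attended), the primary objective and prior attendance in Design 5 are untouched.

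**What to change.** 1. Remove the effect of invitation from Design 5, in both Statistical methods and Exposure opportunity (frequency) bias. Keep attendance before the index screen.
2. Move the total number of invitations from the exposure list to a descriptive check of the matching, or state that its odds ratio is not to be read as an invitation effect.
3. Reconcile the Design 5 control rule: same year in Table 1 and the bias section, same screening interval in Statistical methods.

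These are wording changes with no new data.

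If an invitation effect is still wanted, it needs a separately justified control set not matched on year of first invitation. A tempting route is to drop the year and area matching, let the staggered 2006–2010 roll-out supply the contrast, and adjust for deprivation and region. It should not be adopted in that form. Coverage was national by 2010; if one further two-year cycle reached nearly everyone eligible, there would be little contrast in prior invitation left by the main phase, which follows the 2012–2013 pilot. Adjusting for region would remove much of what the roll-out supplies. Losing area matching is a real trade-off. The 70% in the working is for the invitation count and does not show that such a draw would work for prior invitation in Design 5.

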## Discussion

This study protocol addresses the central question of the effects of the NHS BSCP in terms of the benefits on incidence of advanced primary colorectal cancer, defined as pathological Duke’s stage B or worse using a retrospective matched case–control study approach.

The attraction of the case–control evaluation strategy resides in that for a study nested within the cohort of individuals offered screening, with screening exposure data prospectively recorded, this design confers a reliability and an interpretability comparable with those of a prospective evaluation, while being quick to perform as it requires no further follow-up. It also directly relates the clinical endpoint to the screening history at an individual level, and it requires a relatively small number of cases and corresponding controls. In addition, the case–control design allows the assessment of what actually happened in the population during service screening, taking into account natural variation. It also has the flexibility to question aspects of the screening regime, for example in relation to intervals and target populations, which were not possible to address using RCT data.

The case–control design is potentially prone to a number of biases, in particular some that could confer a bias *in favour* of screening. However, with careful design and analysis, one can minimize the risk of biased results.

When the programme is mature, new case–control studies will be designed to assess the impact of the programme on mortality from colorectal cancer.

### Ethics

The study protocol was reviewed by the NHS BCSP Evaluation Group and approved by the UK Department of Health. The study protocol was submitted to the Health Research Authority (HRA) NHS Health & Social Care Research & Development Ethics Committee (REC) and to the Confidential Advisory Group (CAG, formerly the National Information Governance Board for Health & Social Care (NIGB) via e-submission through the Integrated Research Application System (IRAS). Ethical approval was obtained from the London City & East National Research Ethics Committee (reference number 14/LO/0826), and permission to process identifiable information of patients in England without consent (under section 251 of the NHS Act 2006) was obtained from the CAG (reference number 14/CAG/1020).

## Abbreviations

CRA: Colorectal adenoma
CRC: Colorectal cancer
FIT: Faecal immunochemical test
gFOBt: Guaiac faecal occult blood test
HSCIC: Health & social care information centre
IMD: Index of multiple deprivation
NCDR: National cancer data repository
NHAIS: National health application & infrastructure services
NHS BCSP: NHS bowel cancer screening programme
NHS BSP: NHS breast screening programme
NHS CSP: NHS cervical screening programme
NYCRIS: Northern and Yorkshire Cancer Registry and Information Service
PCDP: Pre-Clinical screen-Detectable Period
PRU: Policy Research Unit in Cancer Awareness, Screening and Early Diagnosis
RCT: Randomised controlled trial.
